## Abstract

**Background:**

The identification of moderators of exposure-based cognitive behavioral therapy (EXCBT) outcomes has the potential to (1) guide the judicious application of the limited resource that is EXCBT and (2) identify additional treatment targets for ameliorating the deleterious effects of an identified moderator, thereby enhancing clinical response. Experimental and clinical studies have yielded intriguing findings for the moderating influence of positive affect on EXCBT outcomes. Mixed findings for state positive affect (at the time of extinction or exposure trials) as a predictor of EXCBT outcomes stand in contrast to evidence that baseline levels of trait positive affect may be a more effective predictor. As such, questions remain about the best way to assess positive affect as a potential treatment moderator.

**Objective:**

This study was designed to investigate (1) the relative value of state and trait positive affect for predicting the outcome of a single-session virtual reality exposure intervention for public speaking anxiety in adults attending college and (2) the role of 3 related constructs—optimism, hopefulness, and mental health self-efficacy—that may explain the predictive significance of trait positive affect.

**Methods:**

State affect will be manipulated at an experimental level using affect induction procedures; trait positive affect will be measured at baseline. Three dependent measures—a primary outcome of public speaking anxiety and secondary outcomes of social phobia and self-reported valence—will be examined. This study relies on a team science approach and is being conducted across 12 collaborating sites through the Exposure Therapy Consortium, allowing for replication of all findings across diverse study sites worldwide.

**Results:**

Data collection for this study began in October 2024 and ended in August 2025. We expect to complete data analysis and submit results for publication in approximately November 2025.

**Conclusions:**

This study will help clarify the relationship among positive affect (state and trait), exposure learning, and 3 related constructs (optimism, hopefulness, and mental health self-efficacy). These findings will illuminate strategies for future treatment improvement and enhanced efficacy.

## Introduction

### Background

Exposure-based cognitive behavioral therapy (EXCBT) is an efficacious first-line treatment for anxiety-related disorders (ie, anxiety, obsessive-compulsive, and trauma- and stressor-related disorders) [1-6]. However, despite its clear efficacy, a substantial minority of patients fail to respond adequately to EXCBT [7-9], continuing the distress and loss of productivity associated with these disorders [10-12]. These limitations on efficacy have motivated the study of extinction learning processes and potential moderators of these processes to better understand, strengthen, and target EXCBT efficacy [7,9].

One such moderator of interest is the affective context of the exposure. In a comprehensive review of the potential of positive affect for improving EXCBT outcomes, Zbozinek and Craske [13] considered the potential beneficial effects of positive affect on core processes linked to extinction learning and retention: attention, encoding, rehearsal, consolidation, retrieval, and stimulus valence. Empirical tests of these ideas have been ongoing. Initial significant findings have been observed for experimental paradigms where positive versus neutral affect were induced [14] or naturally occurring positive affect was examined [15] for predicting better fear conditioning outcomes. However, beneficial effects for positive versus negative affect induction before extinction learning trials were not replicated by Fitzgerald [16] using a fear conditioning paradigm or by van Veen et al [17] using 2-session virtual reality (VR) exposure for participants with high public speaking anxiety. Failures to observe a beneficial effect for preexposure positive affect have also been reported in studies examining extant levels of positive affect in individuals undergoing treatment [18,19].

One possible explanation for these inconsistent findings is that positive affect needs to be experienced across multiple phases of exposure learning, that is, before, during, and after exposure, when the therapeutic memory is consolidated or reconsolidated (eg, when reflecting on the exposure or during between-session exposure practices) [20]. If this explanation is accurate, trait positive affectivity should be a better predictor than state positive affectivity because it has the opportunity to exert its hypothesized effects at multiple phases of the exposure learning process. Results of predictor analyses from 2 clinical trials support this hypothesis [21]. These studies by Taylor et al [22,23] used a measure of trait positive emotionality drawn from the extraversion domain of the NEO Five-Factor Inventory (NEO-FFI) [24], and both studies predicted a significantly better response to cognitive behavioral therapy.

However, trait positive affect is arguably a broader assessment domain than state affect, as reflected by the nature of the assessments used by Taylor et al [22,23]. Specifically, in their first study, Taylor et al [22] used an 8-item positive emotion scale from the extraversion domain of the NEO-FFI, with items reflecting levels of happiness, joy, excitement, and optimism characteristic of one’s personality. The second trial [23] used a shortened assessment: a 4-item positive emotion scale again derived from the extraversion domain of the NEO-FFI. Although Taylor et al [22,23] controlled for associations with the broader domain of extraversion and negative mood reflecting depression, potential elements or correlates of trait positive emotionality may help explain the ability of positive emotionality to predict treatment outcomes. For example, there are a number of variables that are correlated with both positive affect and treatment responsivity and outcomes and, hence, may account for the predictive significance of trait positive affect. Specifically, 3 additional variables—optimism, hopefulness, and self-efficacy—emerge as important assessment targets. Each was selected due to its potential to mediate effects of trait positive affectivity on EXCBT, as indicated by significant associations between each of these variables and positive affect in addition to significant associations with adaptive responses to stress, adaptive coping, positive expectancies, and positive treatment outcomes [25-35]. Accordingly, to hone prediction and better understand the nature of trait positive affect as a potential moderator of EXCBT outcomes, it is important to evaluate whether the prediction hypothesized for trait positive affect can be accounted for by related constructs such as state positive affect, optimism, hopefulness, and self-efficacy.

### Study Objectives

This preregistered study is designed to enhance the understanding of positive affect as a potential predictor (moderator) of EXCBT outcomes by examining two related lines of inquiry: (1) Can we confirm that trait positive affect is a better predictor of treatment outcomes than state positive affect? (2) Can the prediction based on trait positive affect be better understood by considering 3 alternative assessment targets: optimism, hopefulness, and self-efficacy? Answering these questions has the potential to hone attention to a correct and specific mechanistic target (trait vs state positive affect) for understanding and prospectively intervening, with individual characteristics predicting nonresponse to EXCBT. Specifically, accurate specification of a marker of relative nonresponse to this treatment can have a public health impact by aiding (1) the judicious application of EXCBT (personalized medicine) and (2) pretreatment efforts to modify the moderator. Indeed, there is preliminary evidence that such affect-focused treatments can be successful [36]. Accordingly, the longer-term potential of this study is to provide additional strategies for the effective use of EXCBT for patients in need.

To assess the relative capacity of state and trait positive affect to predict responsivity to exposure therapy, we will examine both constructs as moderators of the degree of improvement from a single-session virtual reality exposure intervention for public speaking anxiety in college students. We selected public speaking anxiety as the therapeutic target because it is a prevalent concern among undergraduate students [37,38] and because the use of VR exposure has demonstrated efficacy for treating public speaking anxiety and other social anxiety symptoms [17,39,40]. Furthermore, a VR-delivered intervention is also a highly standardized procedure that can be reproduced exactly across participants and sites [40]. Finally, the use of a single-session VR exposure intervention to judge extinction learning approximates the intervention procedures used by van Veen et al [17] in their study of positive affect induction and exposure outcomes, as well as laboratory paradigms [14].

In this study, state affect just before exposure will be manipulated at an experimental level using affect induction procedures. Trait positive affect will be measured at baseline using procedures developed by Taylor et al [23]. Randomized affect induction will be used for two reasons: (1) to allow for comparison to previous studies that used similar methods [14,16,17] and (2) to ensure that state affect at the time of extinction will be distinct from the degree of trait positive affect. In addition, some studies that have found benefits of state positive affect for extinction learning and return-of-fear outcomes have used the Positive and Negative Affect Schedule [14,41] and, thus, may have been influenced by arousal given that the Positive and Negative Affect Schedule includes only high-arousal items [15]. Our inclusion of state arousal based on the Self-Assessment Manikin (see the Methods section) will help address this alternative explanation for conflicting state affect findings and the value of considering trait affect over state measures. Three dependent measures will be examined—a primary outcome of public speaking anxiety and secondary outcomes of social anxiety and self-reported valence to giving a speech—measured at the 1-week follow-up as the primary outcome window. Initial analyses will evaluate the capacity of both state and trait positive affect to predict VR exposure outcomes. Subsequent analyses will evaluate the degree to which the predictive value of trait positive affect can be accounted for or improved by considering measures of optimism, hopefulness, and self-efficacy.

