#### Selection and Outcome Variables

The Personal Report of Communication Apprehension, Public Speaking Subscale (PRCA-PS), is a 6-item self-report measure for assessing level of public speaking anxiety; item responses range from 1 (“strongly disagree”) to 5 (“strongly agree”), providing total scores that can range from 6 to 30 [48]. Scores of 18 or higher indicate high- to moderate-severity public speaking anxiety and are used to select individuals for this study at the screening and baseline assessment. In a pilot study for this trial [49], 81.3% of the screened sample responding to advertisements for a public speaking anxiety study scored 18 or higher on the PRCA-PS, consistent with high rates of social anxiety reported for student populations [37,38]. The PRCA-PS serves as the primary outcome at the 1-week follow-up assessment.

The Social Phobia Inventory is a 17-item self-report scale to assess fear, avoidance, and physiological symptoms associated with social anxiety disorder over the previous week [50]. The total score (which can range from 0 to 68) will be used as a measure of social anxiety severity, a secondary outcome variable, and will be assessed at the screening and baseline assessment and 1-week follow-up assessments.

The valence of giving speeches is rated on a scale ranging from −3 (extremely unpleasant) to +3 (extremely pleasant). This measure will be administered at the screening and baseline assessment, immediately after treatment, and at the 1-week posttreatment assessment.

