### In-Person Study Session

The in-person study session lasts approximately 75 minutes and begins with an orientation to the VR device. Participants will put on the headset while sitting in a chair. Participants will be oriented to the VR environment by briefly viewing a 360-degree nature scene. Following VR orientation, participants will be asked to rate their current affect and will then watch 1 of 2 short film clips (totaling approximately 5 minutes) for either positive or negative affect induction, determined via random block assignment (1:1 allocation) using an online tool [63], with a block size of 6 and separate blocks for individuals whose sex assigned at birth was male versus female, as programmed into REDCap. Participants are blind to hypotheses. Film clips are shown on a separate laptop or tablet screen. Film clips for positive affect induction were sourced from the movie *Wall-E* and from the television show *Whose Line Is It Anyway?* The film clips for negative affect induction were sourced from the movies *Bambi* and *The Champ*. Studies have demonstrated that each of these film clips is effective in eliciting the targeted affect [64-67]. Before viewing the film clips, participants will be provided with the following instructions: “Let yourself experience whatever emotions you have, as fully as you can. Don’t try to hold back or hold in your feelings.” Participants rerate their state affect following their randomized affect induction procedures.

Following affect induction and subsequent state affect ratings, participants will be shown a prerecorded exposure therapy instruction provided by a therapist from within the VR headset. Participants undergo 6 exposure trials wherein they give a speech to a virtual audience of 6 individuals sitting in chairs around a conference table or in a lecture hall in the 360-degree VR environments [68]. The topic for the speech is “something you’re proud of.” Following exposures, the VR therapist congratulates the participant and provides a short debriefing statement. Once they remove the headset, participants will be asked to rate their public speaking anxiety and current valence toward giving a speech.

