## Discussion

The ETC was organized to *generate better data faster* by facilitating larger-scale studies that can be completed without substantial funding due to relatively low burden across multiple collaborating sites [9,47]. Furthermore, the use of a particularly large and diverse sample recruited at study sites reflecting different settings, backgrounds, and cultures addresses both issues of lower power and limited replication that have characterized the study of the influence of state and trait positive affect on extinction or EXCBT outcomes [13-19,21-23]. The findings being achieved across the various sites in this trial will provide a perspective on their robustness. In addition, although power to detect specific site differences is limited across a 12-site study, discussions of results will be summarized in relation to an ICC used to describe the amount of variability in prediction that can be attributed to cross-site differences.

A limitation of this study is the focus on the potentially homogeneous population of undergraduate students with high public speaking anxiety; the degree to which our results will fully generalize to a clinical population is not known. Accordingly, although this trial will provide a well-honed test of the role of positive affectivity in response to a well-defined exposure therapy intervention, replication of these methods will be needed for clinical samples. This study also relies on self-report instruments without the use of performance or physiological outcomes. This study is designed to address the influence of positive affectivity on acute (1 week) exposure outcomes; the influence of exposure on the maintenance of treatment gains awaits future study.

The accurate identification of markers of EXCBT’s acute efficacy is important given that EXCBT is a limited resource, with evidence that only a minority of individuals receive EXCBT for anxiety-related disorders despite its status as a first-line treatment 69-71]. This study was designed to provide guidance on the role of positive affect in treatment response to aid personalized medicine decisions, including, perhaps, pretreatment efforts to modify the moderator [36,67,68].

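### Trait positive affect is called a moderator of exposure benefit, but everyone is exposed, so the design can show only that it predicts the 1-week score

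*Protocol article*

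**What the plan says.** Study Objectives treats predictor and moderator as one term and states that "we will examine both constructs as moderators of the degree of improvement from a single-session virtual reality exposure intervention for public speaking anxiety". It links the result to deciding who should receive exposure therapy and to changing the moderator before treatment, on the ground that "accurate specification of a marker of relative nonresponse to this treatment can have a public health impact". The Discussion repeats the aim: "to provide guidance on the role of positive affect in treatment response to aid personalized medicine decisions". Data Analysis states the power of the study for moderation effects.

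The design is in In-Person Study Session. All attendees are exposed: "Participants undergo 6 exposure trials wherein they give a speech to a virtual audience". Allocation, 1:1, is only to a positive or a negative film clip. The abstract says that "trait positive affect will be measured at baseline"; it is not assigned.

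Selection and Outcome Variables makes the PRCA-PS both the entry criterion and the 1-week primary outcome: "Scores of 18 or higher indicate high- to moderate-severity public speaking anxiety and are used to select individuals for this study". Table 1 and In-Person Study Session show that the visit rating of speaking anxiety follows the exposures, so the screening score is the only pre-exposure value.

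Data Analysis names linear mixed models and refers to the preregistered plan for the specific tests. It does not say whether the 1-week score is analysed adjusted for baseline, as change, or unadjusted.

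**The concern.** Moderation of an exposure effect means that the difference between exposed and unexposed people varies with trait affect. With no unexposed comparison, that difference is not observed at any level of trait affect. No analysis plan, shown or not, can supply it.

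What remains is prognosis among the exposed. Cheerful students may score lower a week later because they benefited more from exposure, or because they were less anxious than one error-prone screening score suggested. The second explanation needs no treatment effect and has the sign of the hypothesis. The same holds for optimism, hope and self-efficacy if they too correlate negatively with speaking anxiety. At stake is the step from a coefficient in exposed students to a marker for allocating treatment.

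**Working it through.** **The article's own figure.** Data Analysis gives detectable moderation effects of d=0.36 to 0.48 for 12 sites of 40 to 80 (N=480 to 960) at ICC up to 0.05. It does not say which contrast this refers to. I used d = k(1.960+0.842)/√N × √(1+(m−1)ICC), with m per site, k=2 for a two-group contrast and k=4 for a two-by-two interaction.

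- k=2: 0.26 (m=40) and 0.18 (m=80) at ICC 0; 0.44 and 0.40 at ICC 0.05.
- k=4: 0.51 and 0.36 at ICC 0; 0.88 and 0.81 at ICC 0.05.

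No variant reproduces 0.36 to 0.48 over the stated range. Nothing below depends on it. Whatever contrast it refers to, it cannot be exposure by trait affect.

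**Null model.** No exposure effect and no true change. Screening score Y0 and 1-week score Y1 share a true score and carry independent errors. Each has variance 1, and their correlation is the reliability λ. Trait affect X correlates r with the observed score. From the documents: N=480 or 960, α=.05 (taken as two-sided), and 81.3% of the pilot screening sample at or above the cut. Assumed, because the article gives neither: λ=0.7 to 0.9 and r=−0.2 to −0.3. Site effects are left out.

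**Y1 adjusted for Y0.**

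- Slope of X = r(1−λ)/(1−r²).
- Partial correlation = r(1−λ)/√[(1−r²)(1−λ²)].

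At λ=0.8, r=−0.3 the slope is −0.06/0.91 = −0.066 and the partial correlation is −0.06/√(0.91×0.36) = −0.105. By Fisher's z, 0.105×√476 = 2.29, so the test rejects in 63% of trials at N=480; the same step gives 90% at N=960.

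**Change score Y1−Y0.** Without selection, cov(X, Y1−Y0) = r−r = 0 and the rate is 5%. Truncating Y0 to its top 81.3% (cut −0.889) leaves a variance v=0.597. The slope becomes [(1−λ)/(1−r²)]×[r − rv/(1−r²(1−v))]. At λ=0.8, r=−0.3 this is 0.220×(−0.300+0.186) = −0.025, a correlation of −0.040, and rejection in 14% and 23%.

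| λ, r | adjusted slope | adjusted, N=480 / 960 | change, N=480 / 960 |
|---|---|---|---|
| 0.9, −0.2 | −0.021 | 18% / 30% | 7% / 9% |
| 0.8, −0.2 | −0.042 | 32% / 56% | 9% / 13% |
| 0.8, −0.3 | −0.066 | 63% / 90% | 14% / 23% |
| 0.7, −0.3 | −0.099 | 83% / 98% | 19% / 33% |

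Simulations of the same model gave 17% to 84% and 30% to 99% for the adjusted model, and 6% to 20% and 9% to 37% for change. With r=0 the rate is 5%.

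**What drives each bias.** Selecting on a covariate that is in a correctly specified linear model does not alter the other slopes, so the cut cannot produce the adjusted-model bias. Simulation agrees: at λ=0.8, r=−0.3, rejection is 62%/89% with the cut and 65%/90% without it, equal within simulation error. That bias comes from error in the baseline. The change-score bias comes from the cut: 14%/24% with it and about 6% without it.

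**Average change.** The mean of Y0 above the cut is 0.331 SD. Regression to the mean alone then gives a pre-post d of (1−λ)×0.331/√0.597, which is 0.04 to 0.13 for λ=0.9 to 0.7. The uncontrolled pilot change was d=0.32.

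**The case against.** **Wording.** The article itself glosses predictor as moderator, and Data Analysis describes the tests as prediction. The abstract's conclusions are modest, and the Discussion hedges the pretreatment idea and asks for replication in clinical samples. All this stands: the planned prediction analyses are legitimate, and the allocation language is an aim, not a result. But the stated public-health purpose needs true moderation, and the limitations name the student sample, self-report and short follow-up, not the missing comparison.

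**Selection.** A reader might blame entry on a high PRCA-PS for the large rates. The calculation does not support that. At 81.3% passing the cut is mild, and it affects only the smaller change-score bias.

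**Model and assumptions.** The article does not say that the baseline is adjusted for, and it gives neither reliability nor correlation. Both models must therefore be shown, and no single rate is a forecast. The definition of r also matters: at λ=0.8 and −0.3, correlation with the true score gives 54%/83% instead of 63%/90%.

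**Size.** The spurious slope is only 0.02 to 0.10 SD per SD. The stated d of 0.36 to 0.48 corresponds to r = d/√(d²+4) = 0.18 to 0.23, above the largest spurious partial correlation here, 0.09/√(0.91×0.51) = 0.13. So a large trait association could not come from this source alone within these assumptions; a small significant one could.

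**Trait versus state.** A reader might infer that trait affect is biased, state affect is not, and the comparison is rigged. That is not established. Core Predictor Variables measures state affect by the self-rated SAM pleasure score, which the film determines only in part and which may itself correlate with speaking anxiety. Only the randomised induction contrast is free of this bias. The calculations concern the trait coefficient alone, not the trait-versus-state comparison.

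**Conclusion.** The point holds in a limited form. That trait affect cannot be shown to moderate the effect of exposure follows from the design alone and needs no assumption. That a trait coefficient in the hypothesised direction can arise with no exposure effect needs two conditions: a negative correlation of trait affect with speaking anxiety, and reliability below 1. For the baseline-adjusted model the direction then holds at any values; for change scores it also needs the entry cut.

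The rates illustrate how large the problem could be under assumed inputs. They do not show that a positive trait result would be false. The study remains a sound test of prediction among exposed students and of the randomised induction.

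**What to change.** 1. In the objectives, power statement and conclusions, replace moderator with predictor of 1-week outcome after exposure, for trait affect, optimism, hope and self-efficacy. Keep moderation for induction × trait affect, the interaction that involves a randomised contrast.
2. Drop the inference to allocating exposure therapy.
3. In the Discussion, list the missing unexposed comparison and regression to the mean as limitations.
4. State which form of the primary outcome is modelled, and add one sensitivity analysis that corrects the baseline PRCA-PS for measurement error, with reliability estimated from its six items. Internal consistency misses day-to-day fluctuation, so a lower reliability should be tried as well.
5. Base any statement about state affect that is to be free of this bias on the randomised induction arm, not on the SAM rating.

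The cost is a narrower conclusion, one extra model on data already collected, and a slightly less precise corrected coefficient.
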